### Sample

3.5

The study will be conducted in an advanced hospital where approximately 9–12 stoma surgeries are performed monthly. The sample size was calculated using G*Power 3.1.9.2. The calculation was based on the primary outcome of the study, state anxiety. The effect size was calculated using the State Anxiety Inventory scores reported by Akbayrak and Uslu (2026), who evaluated the effect of preoperative stoma education including a wearable dummy stoma on postoperative stoma‐related anxiety, adjustment, and self‐efficacy. In that study, the mean State Anxiety Inventory scores were 36.24 ± 8.15 in the experimental group and 48.16 ± 10.14 in the control group. Based on these values, the effect size was calculated as *d* = 1.29. Using a two‐tailed independent‐samples *t* test, *α* = 0.05, power (1 − *β*) = 0.99, effect size = 1.29, and an allocation ratio of 1:1, the minimum required sample size was calculated as 46 participants, with 23 participants in each group. Considering a possible 10% attrition rate during follow‐up, including stoma closure, mortality, or participant withdrawal, the total planned sample size was increased to 52 participants, with 26 participants in each group.

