### Evaluation of the Data

3.11

The data obtained from the study will be analysed using SPSS 21 (Statistical Package for the Social Sciences) software. First, the demographic and clinical characteristics of the participants will be summarized using descriptive statistics (frequencies, percentages, means and standard deviations). To assess baseline comparability between groups, independent‐samples *t* test will be used for normally distributed continuous variables, Mann–Whitney *U* tests for non‐normally distributed continuous variables, and chi‐square tests for categorical variables.

The primary outcome of the study is state anxiety measured using the State Anxiety Inventory. Changes in state anxiety scores between the intervention and control groups over time will be evaluated using repeated‐measures analysis of variance (ANOVA), including group, time, and group‐time interaction effects. The secondary outcome of the study is postoperative stoma adaptation measured using the Ostomy Adjustment Inventory. Changes in stoma adaptation scores between groups and across follow‐up measurements will also be evaluated using repeated‐measures ANOVA.

Age, gender, diagnosis, stoma type, baseline trait anxiety scores and baseline state anxiety scores will be prespecified as potential covariates. Baseline comparability between groups will be assessed, and adjusted analyses will be performed where clinically relevant imbalances are identified.

All primary analyses will be conducted according to the intention‐to‐treat (ITT) principle. Missing outcome data will be handled using multiple imputation methods. In addition, a per‐protocol analysis including participants who complete all planned assessments will be conducted as a sensitivity analysis. A significance level of *p* < 0.05 will be accepted in all analyses.

Every effort will be made to minimize missing data throughout the study. Reasons for missing data, participant withdrawals, mortality, and stoma closure will be documented and reported in detail. Results will be reported with 95% confidence intervals, effect sizes, and *p* values. The clinical significance of the findings will also be emphasized.

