## Limitations

5

This protocol has several limitations. First, the demographic characteristics and health status of the patients included in the study may limit the generalizability of the results obtained. In addition, the fact that the data will be collected from a single hospital may also make it difficult to generalize the results. Failure to fully control for external factors (e.g., family support, economic status, etc.) that may affect patients' anxiety levels may also have an impact on the results. Furthermore, excluding patients with a psychiatric diagnosis or those taking psychiatric medication may limit the generalizability of the findings. In addition, participant blinding will not be possible due to the nature of the intervention, which may increase the risk of performance bias. Finally, since it will be a long‐term study requiring follow‐up, patients' stoma may close, they may die, or they may want to drop out of the study during the study period, so there may be missing data.

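### The 'per-protocol' set is a 1-month completer set, and imputation of adaptation scores makes no exception for death and conflicts with the exclusion rule for stoma closure

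*Protocol article*

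**What the plan says.** All references are to the protocol article.

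- **Analysis sets (3.11, Evaluation of the Data).** "All primary analyses will be conducted according to the intention"-to-treat principle. Beside this stands a per-"protocol analysis including participants who complete all planned assessments will be conducted as a sensitivity analysis". No adherence criterion is given.
- **Missing data (3.11).** "Missing outcome data will be handled using multiple imputation methods". No exception is stated. The same section adds: "Reasons for missing data, participant withdrawals, mortality, and stoma closure will be documented".
- **What counts as attrition (3.5, Sample).** The 10% allowance is described as "including stoma closure, mortality, or participant withdrawal", with no split by cause.
- **What counts as missing data (5, Limitations).** The section says that patients' "stoma may close, they may die", and goes on: "they may die, or they may want to drop out of the study during the study period, so there may be missing data".
- **Stoma closure (3.4.2, Exclusion Criteria).** Patients whose stoma is closed while the study is running are listed among those excluded.
- **Timing (3.9, Data Collection, and Table 1).** State anxiety is measured 24 h before surgery and on the morning of surgery. Stoma adaptation is measured at discharge and at 1 month (±7 days).

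**The concern.** There are two separate problems, and each affects a different outcome.

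**Anxiety.** A per-protocol set should contain patients who received what they were allocated. This one contains patients who attended everything. Because the primary outcome is finished before surgery, membership depends on events that come after the outcome: surviving, keeping the stoma and attending at 1 month. It also ignores whether the bag was worn. The sensitivity analysis therefore tests neither adherence nor the handling of missing anxiety data.

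**Adaptation.** A patient who withdraws still has an adaptation status that went unobserved, so imputing it makes sense. A patient who has died has none, so that score is undefined rather than missing. If such scores are imputed, the estimated group difference rests partly on values for patients who cannot have one. With 26 patients per arm, a few such values could matter. For closed stomas the article gives two incompatible instructions, so an analyst cannot tell whether to remove the patient or to impute the score.

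**Working it through.** **1. The plan's own figures (3.5).**

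- Pooled SD = √[(8.15² + 10.14²)/2] = √84.62 = 9.199.
- d = (48.16 − 36.24)/9.199 = 11.92/9.199 = 1.296; the plan uses 1.29.
- At d = 1.29, two-sided α = 0.05 and power 0.99, the normal approximation gives 23 per arm. The noncentral t solution is 23.09, and power at 23 per arm is 0.9898. The stated 46 is therefore reproduced, within rounding.
- 46/(1 − 0.10) = 51.1, so 52, as stated.

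**2. Who is in which set for anxiety.** Baseline assessment precedes opening of the envelope (3.6, Randomization), so every randomised patient should have the first state score.

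| Patient | Both anxiety scores | ITT | Plan's 'per-protocol' | Set based on allocated procedure |
|---|---|---|---|---|
| Wore bag to the morning; died before 1 month | yes | in | out | in |
| Wore bag to the morning; withdrew after surgery | yes | in | out | in |
| Took bag off early; attended every visit | yes | in | in | out |

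The plan's set is wrong in both directions. The third row is realistic: 3.8.2 foresees that the simulation may be discontinued in some patients.

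The set is also ambiguous at the edge. Table 1 marks trait anxiety on the morning of surgery, whereas 3.9 names only the state scale there, so it is unclear what completing every assessment requires.

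**3. Size for anxiety.**

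- Patients dropped at the planned attrition: 52 × 0.10 = 5.2, leaving 46.8. This is an upper figure for 10% attrition, because it assumes that every loss falls after surgery.
- Power of a two-sample t test at d = 1.29: 0.995 with 26 per arm, 0.991 with 26 × 0.90 = 23.4 per arm.
- Assumed range of attrition, 5% to 30%: 2.6 to 15.6 patients dropped, power 0.993 to 0.966.

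The cost lies in which patients are selected, not in precision.

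**4. Adaptation, section by section.**

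| Event | 3.5 Sample | 5 Limitations | 3.11 Evaluation | 3.4.2 Exclusion | Result |
|---|---|---|---|---|---|
| Withdrawal | attrition | missing data | imputed | not listed | ordinary missing data; imputation is reasonable |
| Death | attrition | missing data | imputed, no exception | not listed | literal reading imputes a score that does not exist |
| Stoma closure | attrition | missing data | imputed, ITT | excluded | contradictory |

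**5. Number of undefined scores.** The documents do not split the 10%. If all losses are withdrawals, the number of patients affected is 0. If all are deaths or closures, it is about 5. Nothing in the article narrows this range.

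**The case against.** - **The primary result is not at stake.** This stands. The completer set enters only a sensitivity analysis, the primary analysis is ITT, and the imputation question concerns only the secondary outcome.
- **The article says openly who is in the set, so this is mostly a label.** Partly right: no reader is misled about its membership. But the label promises an adherence check that the set cannot give, and for anxiety the rule removes patients with nothing missing.
- **Imputation details belong in an analysis plan that is not shown.** True of the imputation model. The point here rests on what the article does state: missing outcomes are imputed, and death leads to missing data. Separate reporting of deaths and closures is promised, but that does not take them out of the imputation.
- **A reader might infer that the plan imputes adaptation scores for patients who no longer have a stoma.** The documents do not support this, because 3.4.2 excludes patients whose stoma closes. What they support is a conflict between that exclusion and 3.5, 3.11 and 5.
- **A reader might infer that about 10% of the 1-month adaptation scores would be undefined.** This is not supported either. The 10% includes withdrawals, for which imputation is legitimate, and the split is not given.
- **Restricting adaptation to patients alive with a stoma also conditions on post-randomisation events.** This stands. The restriction gives a defined quantity but not a fully randomised comparison, and the plan should say so.

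**Conclusion.** The point holds within limits, and it should be settled before recruitment opens, planned for January 2, 2027 (3.1).

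For anxiety, the set called per-protocol is a completer set. It drops at most about 5 of 52 patients with complete primary data, assuming the planned 10% attrition with every loss after surgery, and it keeps patients who did not receive the simulation as planned. Power at d = 1.29 moves only from 0.995 to 0.991. The ITT primary analysis is unaffected, provided that the closure exclusion is not used to remove randomised patients from it.

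For adaptation, the literal reading sends deaths to imputation. For closures the article contradicts itself. The number of patients concerned is unknown, from none to about 5 at 10% attrition.

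**What to change.** 1. **Per-protocol set for anxiety (3.11).** Define it as randomised patients with a morning-of-surgery state score who received their allocated procedure: in the intervention arm, bag still on at the morning removal; in the control arm, no bag.
2. **All-visits set (3.11).** Call it a completer analysis and use it for adaptation only. Align Table 1 with 3.9 on trait anxiety, so that completion is unambiguous.
3. **Imputation of adaptation (3.11).** Limit it to patients alive with a stoma at the visit in question. Report deaths and closures by arm. State that the adaptation estimate applies to patients alive with a stoma and therefore conditions on post-randomisation events.
4. **Stoma closure (3.4.2 against 3.5, 3.11 and 5).** Reconcile these sections so that a closure after randomisation does not remove the patient from the anxiety analysis.

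**Cost.** Mostly wording, with no change to the sample size. It is not wording alone: item 3 changes what the secondary analysis estimates and must be stated as such. Item 1 needs one recorded item, whether the bag is still on. The forms described do not mention it, but it can be seen when the bag is removed on the morning of surgery (3.8.2).

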### Ethical Approach

3.12

Ethical approval was obtained from the Kocaeli University Non‐Invasive Clinical Research Ethics Committee (14 Dec 2023 approval number: KÜ GOKAEK‐2023/20.19, project number: 2023/410). Patients will be informed that the answers given and all written information will be kept by the researchers; their answers will remain confidential and used only for scientific purposes. Patients will also be informed that they can leave the study at any time. Owing to the low‐risk nature of the intervention and the single‐center design of the study, an independent data monitoring committee will not be established. All study procedures will be carried out in accordance with the ethical standards of the Declaration of Helsinki; patients included in the study will be informed about the study, and verbal and written consent will be obtained. Patients participating in the study will be asked to sign an informed consent form stating that they have been informed and are volunteers.

## Discussion

4

In stoma care, some studies have contributed to the professional development of stoma care nurses or nurses with simulation‐based training (Almeida et al. 2021; MacLean and Patton 2024). In addition, stoma simulation is included in the education of nursing students who will be future nurses (Lucena et al. 2023). To increase the empathy of nursing students and evaluate their thoughts about patients with stomas, a stoma simulation was performed by placing a stoma bag in the abdomen of the students, and the results were evaluated (Karaveli and Demirarslan 2021). Studies have shown that simulation is an effective training method. However, studies with patients are limited. Pouresmail et al. (2019) evaluated the effect of a stoma simulation device on patients' postoperative self‐efficacy. Although this training affects self‐care/self‐efficacy because patients already have a stoma after surgery, routine stoma care may also have an effect. As suggested in this study, a physical stoma simulation is needed for patients' first encounter with the stoma. This study protocol aims to contribute to the limited literature on preoperative stoma simulation in patients undergoing stoma surgery.

## Limitations

5

This protocol has several limitations. First, the demographic characteristics and health status of the patients included in the study may limit the generalizability of the results obtained. In addition, the fact that the data will be collected from a single hospital may also make it difficult to generalize the results. Failure to fully control for external factors (e.g., family support, economic status, etc.) that may affect patients' anxiety levels may also have an impact on the results. Furthermore, excluding patients with a psychiatric diagnosis or those taking psychiatric medication may limit the generalizability of the findings. In addition, participant blinding will not be possible due to the nature of the intervention, which may increase the risk of performance bias. Finally, since it will be a long‐term study requiring follow‐up, patients' stoma may close, they may die, or they may want to drop out of the study during the study period, so there may be missing data.

## Conclusion

6

This study protocol is expected to provide evidence regarding the potential effects of preoperative stoma simulation on patients' anxiety levels and postoperative stoma adaptation. If effective, preoperative stoma simulation may support patients' psychological preparation for surgery and adaptation to life with a stoma. In addition, the intervention may help patients become more familiar with postoperative stoma care and related equipment before surgery. The findings of this study may contribute to the development of supportive nursing interventions for individuals undergoing stoma surgery.

## Ethics Statement

Ethical approval was obtained from the Kocaeli University Non‐Invasive Clinical Research Ethics Committee (14 Dec 2023‐approval number: KÜ GOKAEK‐2023/20.19, project number: 2023/410). Patients will be informed that the answers given and all written information will be kept by the researchers; their answers will remain confidential and used only for scientific purposes. Patients will also be informed that they can leave the study at any time. Owing to the low‐risk nature of the intervention and the single‐center design of the study, an independent data monitoring committee will not be established. All study procedures will be carried out in accordance with the ethical standards of the Declaration of Helsinki; patients included in the study will be informed about the study, and verbal and written consent will be obtained. Patients participating in the study will be asked to sign an informed consent form stating that they have been informed and are volunteers. Information about the study was uploaded to the Clinical Trials platform, and a Clinical Trials ID number was obtained. Clinical Trials ID: NCT06737887.

## Data Availability

Owing to ethical constraints, this study's data are not publicly available. They are available upon request from the corresponding author.
